### Statistics and sample size

The required simple size to detect a difference of 15 % in the frequency of patients that get at discharge a functional improvement greater than 10 points in Barthel Index is 161 patients in each group. Assuming a loss of 15 % of patients in the follow-up, we fixed a final sample size of 185 patients per group.

In an initial descriptive analysis, for qualitative variables we will calculate frequencies and confidence intervals, and for continuous variables, statistics of central tendency and dispersion such as means, standard error and confidence intervals or median and interquartile range. In order to assess the extent of the therapeutic effect, we will compute for every patient the difference between final and initial level of the outcome variables. Normality of continuous variables will be checked graphically and through K-M and Shapiro-Wilk tests, and their differences between groups by means of parametric tests (T-Tests, ANOVA) or non-parametric tests (Mann–Whitney U, Kruskal- Wallis). A Bonferroni post-hoc test will be used to evaluate statically significant (*p* < 0.05) group and time differences. Associations between clinical and biomechanical tests will be reported by their correlation coefficient (r value), level of significance (p value), and the amount of variance explained (r2 value). Values of r will be used to indicate small (r = 0.10), medium (r = 0.30), and large (r = 0.50) size correlations (i.e., effect size). Finally, the relationship between qualitative variables will be assessed through χ^2^ and Fisher exact tests. The level of statistical significance will be 0.05. Data will be analyzed with SPSS package 21.0

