### Outcome measures

#### Primary outcome

The primary outcome measure is the change in functional and cognitive status during the study period. The functional capacity of patients will be evaluated by the Short Physical Performance Battery (SPPB) [47], which evaluates, balance, gait ability, and leg strength using a single tool. The total score will range from 0 (worst) to 12 points (best). The SSPB test has been shown to be a valid instrument for screening frailty and predicting disability, institutionalization, and mortality. A total score of less than 10 indicates frailty and a high risk of disability and falls. One-point change in the score has clinical relevance [48, 49]. Loss of handgrip of the dominant hand is a useful tool for the measurement of functional capacity. It is a strong predictor of disability, morbidity, and mortality as well as one of the components of Fried’s frail phenotype. Furthermore, the functional status of patients will also be assessed before measurements with the Barthel Index, an international and validated tool of disability. The scores range from 0 (severe functional dependence) to 100 (functional independence) [50]. Gait ability will be assessed using the 6-metre gait velocity test (GVT). Starting and ending limits will be marked on the floor with tapelines for a total distance of 8 m. Participants will be instructed to walk in their self-selected usual pace for two attempts. The results of both trials will be averaged to obtain a single value. The first and last metre, considered the warm-up and the deceleration phases, respectively, will not be included in the calculations of the gait assessment. Dual task conditions (gait evaluation during the simultaneous performance of a cognitive motor action) have recently been recognized as a sensitive assessment method for interactions between cognition, gait, falls and frailty. Changes of gait parameters (i.e., gait velocity and gait variability) while performing a dual task test (dual task cost) could be early predictors of falls risk (50) and useful tools for functional evaluations in frail elderly patients. Exercise can modify dual task cost and consequently fall risk and functional capacity (31). The dual-task paradigm [51] will be used in the 6-m habitual gait velocity test (GVT). Two trials will be performed to assess the gait velocity while performing a verbal or counting task (verbal GVT and counting GVT, respectively). During the verbal dual-task condition (verbal GVT), we will measure the gait velocity while participants are naming animals aloud. During the arithmetic dual-task condition (counting GVT), we will assess the gait velocity while participants are counting backward aloud from 100 by ones. The cognitive score will be measured by counting the number of animals named (dual-task with verbal performance) or determining how many numbers were counted backward (dual-task with arithmetic performance). Isometric upper (right hand grip) and lower limb (right knee extensors and hip flexors) muscle strength will be measured using a manual dynamometer. Maximal dynamic strength will be assessed using the 1RM test in the bilateral leg press, knee extension and bench press exercises using exercise machines (Exercycle, S.L., BH Group, Vitoria, Spain). In the first assessment, the subjects will warm up with specific movements for the exercise test. Each subject's maximal load will be determined in no more than five attempts, with a 3-min recovery period between attempts. After determination of the 1RM values, the subjects will perform ten repetitions at maximal velocity at intensities of 50 % of 1RM to determine the maximum power (w) and the loss of power during the ten repetitions in the leg press machine. The power will be recorded by connecting a velocity transducer to the weight plates (T-Force System, Ergotech, Murcia, Spain). During all neuromuscular performance tests, a strong verbal encouragement will be given to each subject to motivate them to perform each test action as optimally and rapidly as possible. Qualified fitness specialists will individually monitor and carefully supervise all training sessions and provide instruction and encouragement during all sessions. Distribution of the training sessions throughout the day should minimize cumulative fatigue and help to maintain adherence. Adherence to the exercise intervention programme will be documented in a daily register of sessions. Changes in cognitive-affective status after the intervention will be measured using the Mini Mental State Examination, Yesavage GDS and Trail Making Test (Table 3).

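### The change-score tests have no value to use for a patient who dies or cannot be tested, and the article does not say how such patients enter the comparison

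*Protocol article*

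**What the plan says.** All references are to the protocol article.

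- **Effect measure** (Statistics and sample size): "we will compute for every patient the difference between final and initial level of the outcome variables". The section then examines "their differences between groups by means of parametric tests (T-Tests, ANOVA) or non-parametric tests".
- **Sizing** (same section): the trial is sized "to detect a difference of 15 % in the frequency of patients that get at discharge a functional improvement greater than 10 points in Barthel" Index. The number needed "is 161 patients in each group". Then: "Assuming a loss of 15 % of patients in the follow-up", "we fixed a final sample size of 185 patients per group". The control rate, the power and the causes of loss are not given.
- **Primary outcome**: change in functional and cognitive status, assessed with SPPB, Barthel Index, gait velocity, strength and cognitive tests. The lowest SPPB score is 0 and the lowest Barthel score is 0.
- **Secondary outcomes** (after Table 3): mortality is listed separately and is not part of the functional outcome.
- **Schedule** (Study design and setting; Table 1): both arms are assessed at baseline (T1), after the training or control period (T2, at discharge), and one and three months after discharge.

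**The concern.** The article promises a difference for every patient, but a final-minus-initial score does not exist for someone who has died or cannot be assessed. A t-test or a Mann–Whitney test on the differences then runs on the patients who have both values, unless the plan assigns a value to the others. The article assigns none, and the sample size expects a sizeable group without a final value.

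This matters because loss may well be related to outcome here. Patients are 75 or older and acutely ill, the Background names disability and death among the consequences of hospitalization, and the later visits require walking and strength tests. The Discussion also expects the programme to reduce mortality and institutionalization. If that is right, the arms would lose different patients. The resulting bias could go either way: if exercise patients who do badly are missing more often, exercise looks better than it is; if exercise keeps more frail patients alive to be tested, a real benefit is diluted.

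**Working it through.** **1. The plan's own figures.** Inputs from Statistics and sample size: 161 per group, 15% loss, 185 per group.

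- 161 × 1.15 = 185.15, which rounds to the stated 185. (161 / 0.85 = 189.4, so 190 would be needed to keep 161.)
- Expected with a final value: 185 × 0.85 = 157. The design therefore allows for 24 (185 − 161) to 28 (185 − 157) patients per group without one.
- The 161 itself can be reached, for example with 29% v 44%, two-sided 0.05 and 80% power, but those rates and that power are assumptions.

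**2. Possible bias if patients without a final value are dropped.** Assume no true effect: the same response rate p among all randomised patients in both arms. If a fraction d of an arm is lost and all of the lost are non-responders, the observed rate is p / (1 − d). If loss is unrelated to response, the observed rate stays p. The article gives none of the by-arm patterns below; they are assumptions.

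| Assumed loss | p | Observed rates | Spurious gap |
|---|---|---|---|
| 15% in each arm, all non-responders in both | 30% | 0.30/0.85 = 35.3% in both | 0 |
| 10% v 20%, all non-responders | 30% | 0.30/0.90 = 33.3% v 0.30/0.80 = 37.5% | 4.2 points |
| 15% in each arm; one arm half non-responders and half random, other arm random | 30% | 0.30 × 0.925/0.85 = 32.6% v 30.0% | 2.6 points |
| 15% in each arm; one arm all non-responders, other arm random (worst case) | 30% | 35.3% v 30.0% | 5.3 points |
| Same worst case | 50% | 0.50/0.85 = 58.8% v 50.0% | 8.8 points |

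For the worst case, the false-positive rate of a two-sided 0.05 two-proportion z-test with 157 per arm follows from the pooled standard error. At p = 30% the pooled rate is 32.65%, SE = √(2 × 0.3265 × 0.6735 / 157) = 0.053, and the critical gap is 1.96 × 0.053 = 0.104. A mean gap of 0.053 is then declared significant about 17% of the time. At p = 50% the same steps give about 35%. In the half-selective case at p = 30% the rate is about 8%.

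**3. Price of counting every missing patient as not improved.** Assume 30% v 45% among those observed, 15% loss in both arms, two-sided 0.05.

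- 0.30 × 0.85 = 25.5% and 0.45 × 0.85 = 38.25%, a gap of 12.75 points.
- Power with 185 per group is 75.1%; 209 per group would be needed for 80%.
- Over control rates of 25% to 42.5%, power runs from 78.5% to 70.0%.
- With 5% loss instead of 15%, power at 30% v 45% is 81.9%.

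**The case against.** The strongest reply is that the article contains no exclusion rule. It speaks of every patient, and a sample-size allowance for loss is a planning device that is compatible with analysing all randomised patients. The handling of deaths and missing scores usually sits in a full protocol or analysis plan, neither of which is shown, so silence alone is no fault. This stands. A reader might infer that the arms will be compared among survivors only, or that the 15% are mostly deaths and deteriorations; the article says neither.

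A reader might also infer that patients who worsen under training leave the trial by a route closed to controls. The article does not support that either: both arms have the same T1–T4 assessments, and stopping training is not described as leaving the study.

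Deterioration is also not the same as missingness. A worsened patient can still be scored on the Barthel Index and counts as a non-responder, and the SPPB has a floor of 0. The exclusion criteria also rule out terminal illness and unstable disease. The problem is therefore narrower than all bad outcomes: it concerns death before assessment and patients who could not be tested.

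Finally, the 15% is described as loss in the follow-up, which runs to three months, whereas the sizing endpoint is at discharge. Loss at discharge may be smaller, and the 15% rows in the table may overstate the effect on that endpoint.

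What the reply does not remove is that the article goes beyond silence. It names the effect measure and the tests, and those tests cannot include a patient without a final level unless something is added.

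**Conclusion.** The point holds in a conditional form. The method as written yields no value for patients who die before assessment or cannot be tested, and the article does not say how they count. If they are dropped, the arms are compared only among those tested, and the result is biased to the extent that loss relates to outcome differently by arm.

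The size cannot be read from the article. At a 30% true rate the illustrations run from 0 (equal loss for the same reasons), through 4.2 points (10% v 20%, all non-responders), to 5.3 points (one-sided worst case at 15%), against a design difference of 15 points. Equal loss rates alone do not guarantee zero, because the reasons for loss may differ. The 5.3 points, and the 8.8 points at a 50% rate, are upper-end illustrations and not expectations. The article does not support a statement that the trial plans a survivor or completer analysis. This should be settled before analysis.

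**What to change.** State in the analysis section:

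1. The Barthel responder endpoint at discharge is analysed in all randomised patients, in the group assigned, with death before T2 counted as not improved.
2. SPPB is scored 0 when a patient is present but unable to perform it.
3. The change-score test is replaced by a baseline-adjusted repeated-measures model that uses all observed scores.
4. One sensitivity analysis counts every missing Barthel response as not improved. Loss and its reasons are reported by arm.

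The cost is wording, plus recording why a test was not done; the scheduled assessments do not change. Response rates will be lower in both arms. The sensitivity analysis also loses power: about 75% with 185 per group under the assumed 30% v 45%, 15% loss and two-sided 0.05. It should therefore be read as a check on the main result and not as a second primary test.

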**Fig. 1 Fig1:**
[figure not shown]
Flow diagram of the study protocol

**Table 1 Tab1:** Time of measurement of the different variables on the participants of the study

Measurement	T1 Baseline	T2 After training or control period	T3 1-month	T4 3-months
Categorical scale of pain	X	X	X	X
Barthel Index	X	X	X	X
Geriatric depression Scale of Yasavage	X	X	X	X
Mini-Mental State Examination (MMSE)	X	X	X	X
Short Physical Performance Battery (SPPB)	X	X	X	X
Gait Velocity Test (GVT)	X	X	X	X
Dual-task (verbal and counting GVT)	X	X	X	X
Maximal isometric force of handgrip, knee extension and hip flexion	X	X	X	X
1RM (Leg press, Chest press and Knee extension)	X	X	X	X
Muscle power at 50 % 1RM in Leg press	X	X	X	X
Confusion Assessment Method (CAM)	X	X	X	X
Quality of Life (EQ-5D)	X	X	X	X
Geriatrics syndromes	X	X	X	X
Isaacs set test	X	X	X	X
Trail Making Test (TMT)	X	X	X	X
Laboratory parameters	X			
Diseases considered grouped by ACG of Salisbury and CIE-10 codes	X			
Cumulative Illness Rating Scale for Geriatrics (CIRS-G)	X			
Zarit Scale	X			
Falls	X	X	X	X
Mini Nutritional Assessment (MNA)	X			

Adverse events, including muscle pain, fatigue, and general aches and pains will be recorded by the training and testing staff and by self-report during the study period. We will also record the number of falls during the study and for one year prior to admission.

This study has been approved by the Navarra Clinical Research Ethics Committee (Pyto 23/2014).

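### Unadjusted change scores for MMSE and Trail Making lose precision that the baseline score and baseline CAM, both already collected, could recover, and within-arm change cannot be read as cognitive gain

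*Protocol article*

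**What the plan says.** Under *Primary outcome* the protocol states: "The primary outcome measure is the change in functional and cognitive status during the study period". It names the cognitive instruments in the same section: "Changes in cognitive-affective status after the intervention will be measured using the Mini Mental State Examination, Yesavage GDS and Trail Making Test". This point concerns the MMSE and the TMT.

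*Study design and setting* places the initial visit (T1) within the acute hospitalisation, with recruitment starting in the first 48 hours on the ward. Table 1 schedules the row beginning "Confusion Assessment Method (CAM" at T1 and at every later visit, alongside the MMSE and TMT.

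Under *Study participants and eligibility criteria*, the only cognitive exclusion named is severe dementia. Patients must be able to communicate and capable of consent, and the attending physician may exclude for any factor that precludes testing.

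*Statistics and sample size* fixes the effect measure: "we will compute for every patient the difference between final and initial level of the outcome variables". Groups are compared by t-test or ANOVA, or by rank tests, with no covariate named, and differences over time are also tested. Delirium appears in the protocol as a baseline descriptor and a secondary outcome; baseline CAM is not used in analysing cognition.

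**The concern.** A patient who is delirious at T1 scores below their usual level on the MMSE and TMT, and the score recovers when the delirium clears. A raw difference therefore mixes two kinds of patient: a few with large rebounds and many with small changes. The mixture widens the confidence interval on a component of the primary outcome.

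It also raises the average change within each arm without any lasting cognitive gain. That matters because differences over time are to be tested, and because the *Discussion* gives lower cognitive impairment as one of the expected results of changing hospital care.

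The baseline score cannot fully separate the two kinds of patient. A low T1 MMSE may reflect stable impairment, with a small expected change, or delirium, with a large one. Baseline CAM carries that distinction and is already being collected.

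**Working it through.** **The plan's own figures.** The protocol gives no figure for cognitive change or delirium. Its sample size concerns the Barthel Index (to "detect a difference of 15 % in the frequency of patients that get at discharge a functional improvement greater than 10 points in Barthel Index"), and enters here only as a number of patients: 185 per arm less 15 % loss is 185 × 0.85 = 157 per arm.

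**Assumptions (none from the documents).** Stable MMSE variance between patients B = 16 (SD 4); error variance per visit e = 4 (SD 2); a proportion *p* delirious at T1, with the score lowered by *d* points; a fraction *c* = 0.7 cleared by T2; *t* = variance of true change between patients, first set to 0. Write q = p(1 − c).

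**Formulas.**
- Var(T1) = B + e + d²p(1 − p)
- Var(T2) = B + e + t + d²q(1 − q)
- Cov = B + d²q(1 − p)
- Change score: Var(T1) + Var(T2) − 2 Cov
- ANCOVA on the T1 score: Var(T2) − Cov²/Var(T1)
- ANCOVA on the T1 score and CAM: B + e + t + p d²c(1 − c) − B²/(B + e)

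**Example: p = 15 %, d = 5, t = 0.** Var(T1) = 23.19, Var(T2) = 21.07, Cov = 16.96.
- Change score: 23.19 + 21.07 − 2 × 16.96 ≈ 10.35
- T1 score only: 21.07 − 16.96²/23.19 ≈ 8.7
- T1 score and CAM: 20 + 0.15 × 25 × 0.21 − 256/20 = 7.99

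The T1 score cuts the variance by about 16 %; CAM then cuts what remains by about 8 %.

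**Range.** With t = 9, true change has SD 3.

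| p, d | t | Change score | T1 score | T1 score + CAM | Cut by T1 score | Further cut by CAM |
|---|---|---|---|---|---|---|
| 5 %, 3 | 9 | 17.30 | 16.40 | 16.29 | 5.2 % | 0.6 % |
| 10 %, 3 | 9 | 17.59 | 16.58 | 16.39 | 5.7 % | 1.2 % |
| 15 %, 5 | 9 | 19.35 | 17.67 | 16.99 | 8.7 % | 3.9 % |
| 10 %, 3 | 0 | 8.59 | 7.58 | 7.39 | 11.7 % | 2.6 % |
| 15 %, 5 | 0 | 10.35 | 8.67 | 7.99 | 16.2 % | 7.9 % |
| 25 %, 7 | 0 | 15.07 | 11.35 | 9.77 | 24.7 % | 13.9 % |

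The baseline score gives the larger part in every row.

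**Power.** A simulation with 157 per arm, 3,000 runs per setting, 80 % clearing, t = 0 and a true effect of 0.9 MMSE points gave:

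| p, d | Change score | T1 score | T1 score + CAM |
|---|---|---|---|
| none delirious | about 81 % | about 84 % | – |
| 10 %, 3 | 77.0 % | 81.9 % | 83.4 % |
| 10 %, 6 | 68.6 % | 76.1 % | 80.0 % |
| 20 %, 6 | 59.1 % | 70.5 % | 77.7 % |

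**Bias between arms.** In the same simulation the change-score estimate stayed at 0.89 to 0.91 for a true 0.90, and the type I error at 4.2 % to 5.7 %.

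**Change within an arm.** With no true gain, the mean change is p × c × d. At c = 0.8 this is 0.1 × 0.8 × 3 = 0.24 points and 0.2 × 0.8 × 6 = 0.96 points.

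**The case against.** **The comparison between arms is not biased.** A reader might infer that clearing delirium would pass for a treatment effect. It does not: T1 delirium is balanced in expectation by randomisation and its natural clearing cancels between arms. This stands in full. Only precision, chance imbalance and the reading of within-arm change are affected.

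**Eligibility probably removes much delirium.** The communication, consent and testing criteria act as a filter. Scheduling CAM at T1 does not show that delirious patients are expected, since delirium is an outcome and needs a baseline. This stands as a limit on size. It does not make delirium an exclusion, and the protocol provides for relatives to be informed when a patient has cognitive impairment.

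**Double counting.** A reader might infer that, if exercise speeds delirium clearance, one effect would be counted both as cognition and as delirium, and that adjusting for baseline CAM would prevent it. If clearance rose from 60 % to 80 %, the MMSE contrast would be p × 0.2 × d: 0.06 points at 10 % and 3 points, 0.35 at 25 % and 7 points. A baseline CAM covariate leaves that contrast unchanged. Faster clearance would also be a genuine treatment effect, and overlap between a primary and a secondary outcome is not an error.

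**Covariates belong in the statistical analysis plan.** Often so, and that plan is not shown. But the protocol does not stay silent here: it fixes the difference from baseline and the unadjusted tests, and that stated choice is what is questioned.

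**Conclusion.** The point holds as an inexpensive improvement in precision and interpretation. It is not a flaw in the validity of the randomised comparison. The plan fixes a less efficient analysis for the cognitive part of the primary outcome than its own baseline data allow, and changes within an arm or over time should not be presented as cognitive gain.

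The size cannot be settled from the documents. Beyond the baseline score, CAM's contribution runs from about 1 % of residual variance (low prevalence, small drop, true change varying between patients) to about 14 % (25 % delirious, 7-point drop, no variation in true change). The power table uses that last, favourable assumption, so its gains lie towards the upper end. All of these calculations concern the MMSE at T2; nothing was computed for the TMT or for the one- and three-month visits.

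**What to change.** In *Statistics and sample size*, replace the unadjusted difference for the MMSE and TMT at T2 to T4 with ANCOVA, or an equivalent repeated-measures model, with the T1 score and T1 CAM status (positive or negative) as covariates. State that no CAM result after randomisation enters the model, because it may itself be affected by treatment.

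Add a supportive estimate in patients who are CAM-negative at T1. The subset is defined at baseline, so the randomised comparison is kept. Say with it that it does not remove delirium arising after T1, and that faster delirium clearance would be a real effect of the intervention.

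The cost is one or two degrees of freedom and one extra table. No visit, test or patient is added, and if delirium at T1 proves rare the CAM covariate does almost no harm.
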